### Statistical Analysis

Clinical and demographic data between groups of patients (severe vs nonsevere) as well as treatment profiles and differences in successive time points will be compared. To compare mean values of soluble biomarkers between groups, the *t* student test (or analysis of variance with post hoc test for multiple groups) or the nonparametric Mann-Whitney (or Kruskal-Wallis for multiple groups) test will be used as appropriate, according to the observed sample distribution features. The SAS 9.3 software (SAS Institute Inc) will be used with a significance level set at .05. The main binary outcomes will be analyzed by the estimation of relative risks using a log-binomial generalized model or by the area under the curve using trapezoidal methods. All personnel conducting laboratory procedures will be blinded regarding the patient status (severity of COVID-19). Receiver operating characteristic curves will determine cutoff points at which individual or combined scores of the molecular and cellular biomarkers become informative of the progression of COVID-19 cases, according to optimal sensitivity and specificity to identify the signature that best characterize each clinical status.

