### Assessment of Molecular and Cellular Immunological Biomarkers

Serum biomarkers will be assessed using the Luminex Bio-Plex Pro platform set for 27 human immune mediators (Bio-Rad Laboratories, California) for the simultaneous assessment of the following analytes: chemokines (CXCL8, CCL11, CCL3, CCL4, CCL2, CCL5, and CXCL10), proinflammatory cytokines (IL-1β, IL-6, TNF-α, IL-12p70, IFN-γ, IL-17A, and IL-15) and regulatory cytokines (IL-1Ra, IL-4, IL- 5, IL-9, IL-10, and IL-13), and cell growth factors (IL-2, IL-7, FGF-basic, PDGF, VEG, G-CSF, and GM-CSF). All procedures will follow the manufacturer’s recommendations, with levels obtained at days 0, 3, and 9.

The expression levels of immune mediators will be assessed by TaqMan quantitative RT-PCR (qRT-PCR) assays (Applied Biosystems, Foster City, CA) for each transcript, with retro-transcription set up with 1 ng/μL of RNA from PBMCs and from neutrophils. The reactions will be carried out on a QuantiStudio 3 Thermal Cycler (Applied Biosystems, CA) in standard mode [26]. Alternatively, qRT-PCR experiments for selected genes will be based on the SYBR Green (family of dyes for molecular biology) detection methodology using the SYBR Green PCR Master Mix and universal cycling conditions on the ABI Prism 7000 Sequence Detection System. Expression levels will be assessed on days 3 and 9.

Immunophenotypic/functional profiles of circulating leukocytes will be assessed upon short-term culture in vitro. The cell suspension will be stained with distinct panels of monoclonal antibodies comprising CD3, CD4, CD8, HLA-DR, CD25, CD19, CD5, CD27, CD38, PD-1, CD28, CD14, CD16, and CD56 for cell surface analysis, and IL-1β, IL-6, TNF-α, IFN-α, IL-5-PE, and IL-10 for evaluation of intracytoplasmic functional status. Cells will be run on a FORTESSA flow cytometer (BD Bioscience, CA). An average of 100,000 cells will be analyzed per sample. The phenotypic/functional parameters will be assessed using FlowJo software (BD, New Jersey). Leukocyte phenotyping will be obtained at days 0, 3, and 9.

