### Sample Size Calculation

The sample size calculation was based on the assumption that 20% of patients who are critically ill have elevated TNF-α levels compared to 5% of patients who are noncritically ill [8]. TNF levels will be normalized according to the study population. Based on a bilateral 95% significance level, a power of 80%, and a case-control ratio of 1, a sample size of 200 patients can be predicted.

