A metabolomics study of serum from patients with COVID-19 annotated 941 metabolites. The authors identified metabolic patterns in severe cases that could be used to propose diagnostic models capable of predicting progression to severe infection and assist in the treatment strategy [37]. Observed changes in the lipid profile (>100 lipids) cause liver damage, as reflected by abnormal serum levels of bilirubin and bile acids [37]. Another study revealed the consequences of treating patients with SARS-CoV with methylprednisolone. Disturbances in the serum lipid profile 12 years post infection were associated with long-term systemic damage caused by high doses of methylprednisolone [38]. Metabolomics is therefore a powerful tool for identifying and monitoring the prognosis and markers at different stages of a disease, particularly for unknown infections [24].

Similarly, neutrophil functional and molecular assays have been performed in patients with COVID-19 [39], clearly indicating the participation of these cells in the pathogeny, although no specific molecular model has yet been proposed [40]. Therefore, the proteomic approach coupled with further analysis at the transcription and functional level will provide evidence to correlate neutrophil activity to the disease severity and time course.

Only two treatments have shown substantial beneficial effects to date in randomized trials in COVID-19, with both exhibiting heterogeneity of treatment effect between subgroups. A preliminary report from Beigel et al [41] showed that remdesivir shortened the median recovery in a trial from 15 days in the placebo group to 11 days, but those on mechanical ventilation were less likely to benefit. On the other hand, dexamethasone demonstrated a reduction in mortality at 28 days, but mainly in those on mechanical ventilation [42]. One possible explanation for these findings is that an adequate immune response to stop viral replication is needed at the onset of the disease. The excess of inflammation presenting is detrimental. As the time when these treatments are initiated could be key, immune biomarkers that signal phases of disease to guide the timing of treatments could be extremely useful in clinical practice.

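### A single .05 level covers about 145 severity comparisons with no control across markers or days, and the TNF-α comparison that sized the study has no primary role in the analysis

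*Protocol article*

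**What the plan says.** The protocol's Statistical Analysis section compares mean soluble biomarker values between groups by t test or Mann-Whitney, with analysis of variance plus a post hoc test, or Kruskal-Wallis, where there are several groups. It also plans comparisons over successive time points. It then fixes the level: "The SAS 9.3 software (SAS Institute Inc) will be used with a significance level set at .05". It refers to main binary outcomes in the plural without naming them, and does not mention TNF-α.

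The Sample Size Calculation assumes that "20% of patients who are critically ill have elevated TNF-α levels compared to 5% of patients who are noncritically ill". With a two-sided 95% level (read here as .05), 80% power and a 1:1 ratio, it arrives at 200 patients. No sampling day is attached to this comparison.

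The section on molecular and cellular biomarkers describes a "Luminex Bio-Plex Pro platform set for 27 human immune mediators". On timing it says: "All procedures will follow the manufacturer’s recommendations, with levels obtained at days 0, 3, and 9". TNF-α is one of those 27 analytes and also appears among the transcripts and the intracellular markers. The Timeline section samples the T-branch on days 0, 9 and 18 and the D-branch on days 0, 3, 9 and 18.

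**The concern.** A nominal .05 applied marker by marker does not limit how many markers are wrongly reported as differing between mild/moderate and severe/critical disease. The post hoc test does not help: it adjusts among groups once a marker has been chosen, and leaves the number of markers and days untouched.

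The sizing and analysis sections also do not connect. Power was claimed for one binary comparison, but the analysis does not say that this comparison comes first. A reader of the results could not tell which test the 200 patients were recruited to answer. If TNF-α is treated as one of many and the alpha is shared, the claimed power is lost. The Discussion wants the results to serve as a basis for later clinical studies, so an unfiltered list of markers would be carried forward.

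**Working it through.** **1. The plan's own figure.** Inputs from the Sample Size Calculation: p1 = 0.20, p2 = 0.05, two-sided .05, power 80%, 1:1.

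n per group = [1.96·√(2·0.125·0.875) + 0.842·√(0.20·0.80 + 0.05·0.95)]² / 0.15² ≈ 75.1, so 76 per group and 152 in total. With continuity correction it is 88 per group, 176 in total. The stated 200 is not reproduced from the stated inputs. It errs on the large side, and the multiplicity point does not depend on it. With 100 per group, power at .05 is 0.90 (0.88 by Fisher's exact test).

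**2. Counting the severity tests.** The T-branch has no day-3 sample, so severe vs nonsevere can be tested only on days 0, 9 and 18, and only where Table 1 schedules the assay. Marker counts come from Textbox 1. Intracellular markers are taken to follow the phenotyping days. Each listed marker is counted once per shared day. Expected false positives under a global null are 0.05·m. The chance of at least one, if tests are independent, is 1 − 0.95^m.

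| Family | Markers × shared days | m | Expected | At least one |
|---|---|---|---|---|
| Serum mediators | 27 × 2 | 54 | 2.70 | 94% |
| Biochemical tests | 10 × 3 | 30 | 1.50 | 79% |
| Surface phenotyping | 14 × 2 | 28 | 1.40 | 76% |
| Transcripts | 15 × 1 | 15 | 0.75 | 54% |
| Intracellular markers | 6 × 2 | 12 | 0.60 | 46% |
| Hormones | 2 × 3 | 6 | 0.30 | 26% |
| Total | | 145 | 7.25 | above 99% |

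Comparisons between time points within a branch would add further tests and are not counted.

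**3. Sensitivity.** Correlation among mediators, and between days in the same patient, lowers the chance of at least one false positive but not the expected number. The expected number falls in proportion to the share of true nulls: if only half of the 54 serum comparisons are null, it is 0.5 × 2.7 = 1.35.

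**4. What a primary role is worth.** If TNF-α had to share alpha with the other mediators on one day by Bonferroni, its level would be .05/27 = .00185. Power for 20% vs 5% with 100 per group would fall from 0.90 to 0.54, and 80% power would need 302 patients. Named alone at .05, it keeps 0.90.

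**The case against.** The strongest defence is that this is an observational biomarker cohort meant partly to feed later studies, reported in a condensed article. A stated .05 is not a statement that nothing will be adjusted, and an adjustment method may sit in an analysis plan that is not shown. Elevated TNF-α is binary and could be among the unnamed main binary outcomes, so the gap is imprecision rather than contradiction. The Discussion itself cites higher interleukin levels in severe disease, so a global null is an extreme case.

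Much of this is fair, and it limits the size of the point. It does not remove it. The protocol states a level and a multiplicity device, and that device does not address markers or days. The article does not label these tests exploratory. Which comparison is primary is something a protocol should fix.

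Several stronger readings are tempting but unsupported:

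- **A false positive in every panel.** Transcripts, intracellular markers, hormones and the single-day D-dimer each expect fewer than one.
- **Thousands of tests at .05.** Metabolomics goes through MetaboAnalyst and proteomics through in-house R scripts, with no threshold stated, whereas the .05 sentence is tied to SAS. The Discussion does say "A metabolomics study of serum from patients with COVID-19 annotated 941 metabolites", but that is another study's count. Selected metabolites are also to be re-measured by targeted assay.
- **81 serum severity tests, counting day 3.** The T-branch has no day-3 sample.
- **Markers below .05 passing into the signature.** The signature is described through receiver operating characteristic cutoffs, and no p-value filter is stated.

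**Conclusion.** The point holds for the SAS-analysed marker comparisons. The serum panel alone carries it: 54 severity tests, 2.7 expected false positives under a global null, and up to a 94% chance of at least one. Over all listed non-omics markers the count is about 145 tests and about 7 expected.

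These figures assume one test per marker per shared day, the .05 rule applied to each listed family, and no true differences. The 94% also assumes independence and is therefore an upper figure for positively correlated markers. The power figures assume 100 patients per group.

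Separately, the comparison that justified the sample size has no stated primary role. This should be corrected before the main analysis. It does not invalidate the design, and it says nothing about the metabolomic or proteomic results.

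**What to change.** In Statistical Analysis, name the proportion with elevated serum TNF-α, severe vs nonsevere, at one prespecified shared day (for example day 0) as the single primary comparison at two-sided .05. Keep the binary form used for sizing, and state in advance what counts as elevated. Label the other marker comparisons exploratory. Apply the Benjamini-Hochberg procedure at a 5% false discovery rate within each assay family, and report q-values with effect estimates.

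The Results section says that data analysis starts only after inclusion data are complete, so for the main analysis the change can still be prospective. The coagulation branch is already complete with preliminary results seen, so any adjustment there should be reported as post hoc.

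The cost is a few sentences and routine software output. The downside is that fewer markers will be called significant.

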**Methods:**

To accomplish these aims, we will analyze demographic characteristics, biochemical tests, immune biomarkers, leukocyte phenotyping, immunoglobulin profile, hormonal release (cortisol and prolactin), gene expression, thromboelastometry, neutralizing antibodies, metabolic profile, and neutrophil function (reactive oxygen species production, neutrophil extracellular trap production, phagocytosis, migration, gene expression, and proteomics). A total of 200 reverse transcription polymerase chain reaction–confirmed patients will be enrolled and divided into two groups: mild/moderate or severe/critical forms of COVID-19. Blood samples will be collected at different times: at inclusion and after 9 and 18 days, with an additional 3-day sample for severe patients. We believe that this information will provide more knowledge for future studies that will provide more robust and useful clinical information that may allow for better decisions at the front lines of health care.

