**Gene expression assays**
IFN-γ, IL-12, IL-17a, TNF-α, IL-6, IL-4, IL-5, IL-10, IL-1b, RANTES, MCP-1, MIP, MIG, IP-10, and IL-8

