**Leukocyte phenotyping**
CD3, CD4, CD8, HLA-DR, CD25, CD19, CD5, CD27, CD38, PD-1, CD28, CD14, CD16, and CD56

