**Leukocyte functionality**
IL-1β, IL-6, TNF-α, IFN-α, IL-5-PE, and IL-10

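### Biomarker cutoffs and signatures are optimised in the one cohort of 200 with no internal validation named, so accuracy read from that fit would be too high, mainly for combined or selected scores

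*Protocol article*

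**What the plan says.** The Statistical Analysis section of the protocol article fixes how cutoffs and signatures are chosen: "Receiver operating characteristic curves will determine cutoff points at which individual or combined scores of the molecular and cellular biomarkers become informative", and this is done "according to optimal sensitivity and specificity to identify the signature that best characterize each clinical status".

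The data come from a single cohort. The abstract states "A total of 200 reverse transcription polymerase chain reaction–confirmed patients will be enrolled and divided into two groups", and Sample Size Calculation uses a ratio of 1, so 100 per group is the planned split.

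The candidates are many:

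- The serum panel is "set for 27 human immune mediators".
- The gene expression list has 15 transcripts: "IFN-γ, IL-12, IL-17a, TNF-α, IL-6, IL-4, IL-5, IL-10, IL-1b, RANTES, MCP-1, MIP, MIG, IP-10, and IL-8".
- The leukocyte list has 14 surface markers: "CD3, CD4, CD8, HLA-DR, CD25, CD19, CD5, CD27, CD38, PD-1, CD28, CD14, CD16, and CD56".
- The functional list has 6 intracellular markers: "IL-1β, IL-6, TNF-α, IFN-α, IL-5-PE, and IL-10".

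That makes 27 + 15 + 14 + 6 = 62 named candidates, before hormones, proteomics, metabolomics and repeated time points.

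No section names a data split, cross-validation, bootstrap correction, a cutoff fixed in advance or a second cohort. Metabolomic Profiling does speak of validation, but there it means testing metabolite differences between groups and quantifying selected metabolites with a targeted assay. Neither tests a score or a cutoff.

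**The concern.** A cutoff placed where sensitivity and specificity look best, on a score whose markers and weights were fitted to the same patients, fits chance features of those patients. Performance measured on them is then higher than it would be in new patients. The gap grows with the number of candidates searched or combined relative to the size of the smaller group.

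The Statistical Analysis section makes this optimised result the criterion for calling a score informative, and nothing in it labels the cutoffs exploratory or the accuracy apparent. The Discussion presents the biomarkers as possible prognostic tools and hopes that later clinical work will build on the study's results. Overstated accuracy and unstable cutoffs could be carried into that work and fail to replicate.

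**Working it through.** **Inputs from the article.** 27 serum mediators (Assessment of Molecular and Cellular Immunological Biomarkers); 200 patients at ratio 1 (Sample Size Calculation); 85 severe/critical and 30 mild/moderate patients enrolled by the end of July 2020 (Results). The article states no accuracy figure for any signature, so there is none to reproduce. Its 200 was sized on elevated TNF-α in 20% against 5% of patients and serves here only as the cohort size.

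**Assumptions, not in the article.** Independent normal markers; markers ranked by AUC; a linear combination (logistic or linear discriminant); the cutoff that maximises sensitivity + specificity − 1; evaluation on the same patients.

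**Step 1: pure noise, 100/100, by simulation (300 to 600 replicates per setting).**

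| Score | Apparent AUC | Apparent sensitivity / specificity | AUC in new patients |
|---|---|---|---|
| One prespecified marker | 0.53 | 0.55 / 0.56 | 0.50 |
| Best single of 27 | 0.59 | 0.60 / 0.60 | 0.50 |
| Top 5 of 27 | 0.65 | 0.63 / 0.64 | 0.50 |
| All 27 | 0.71 | 0.67 / 0.68 | 0.50 |

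**Step 2: check by formula.**

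- Under no association the standard error of an AUC is √[(n₁+n₀+1)/(12·n₁·n₀)] = √(201/120,000) = 0.041.
- One marker, with its direction chosen from the data, has mean 0.5 + 0.798 × 0.041 = 0.53.
- For the best of 27, the median of the largest |z| solves (2Φ(z) − 1)²⁷ = 0.5, so z ≈ 2.24 and the AUC is 0.5 + 2.24 × 0.041 = 0.59.
- For all p = 27 combined linearly, with N = n₁ + n₀, the expected apparent squared distance between groups is D² = p(1/n₁ + 1/n₀)(N − 2)/(N − p − 3) = 27 × 0.02 × 198/170 = 0.629. Then AUC ≈ Φ(D/√2) = Φ(0.793/1.414) = Φ(0.561) = 0.71.

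**Step 3: real signal, 100/100.** With a true AUC of 0.85, apparent AUC minus new-patient AUC is about 0.02 for a selected top 5 and about 0.09 for all 27. Under pure noise the all-27 gap is 0.71 − 0.50 = 0.21. The 0.02 applies when a few markers carry the signal; the gap for a top 5 is larger if the signal is spread thinly over many.

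**Step 4: unequal groups.**

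- At the enrolled 85/30, noise gives 0.64 (best single), 0.73 (top 5) and 0.81 to 0.82 (all 27). The formula agrees for all 27: 27 × (1/85 + 1/30) × 113/85 = 1.62, and Φ(1.272/1.414) = 0.82.
- Part of that rise reflects the smaller total of 115. If the same ratio is projected to 200 (200 × 85/115 ≈ 148, leaving 52; an assumption), all 27 give 27 × (1/148 + 1/52) × 198/170 = 0.817, and Φ(0.904/1.414) = 0.74.

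**Step 5: does the remedy work?** Five-fold cross-validation with marker selection inside the folds returns the noise scores at 100/100 to 0.495 (top 5) and 0.497 (all 27).

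**Step 6: correlated markers.** With pairwise correlation 0.5 the all-27 figure at 100/100 stays at 0.71, because a linear fit is unchanged by re-mixing its predictors. The top-5 figure falls from 0.66 to 0.62.

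**The case against.** The strongest reply is that this is one paragraph of a condensed article. Choosing an ROC cutoff by sensitivity and specificity is ordinary practice, and the resampling scheme, penalty and interval method usually belong in the full protocol or analysis plan, which is not shown. This stands in part. The absence of a named bootstrap would not be a finding alone. The article does, however, state the selection rule and makes its optimised result the test of being informative, and that rule, followed as written, yields optimistic accuracy.

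A reader might infer that the article commits to reporting in-sample accuracy. It does not say so. That is an inference from a single cohort with no validation step named.

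A reader might also infer that a signature of pure noise would be presented as useful. The article does not support that either. It specifies neither a 27-marker unpenalised model nor any other combination rule, and it cites published associations between such mediators and severity, so pure noise is the worst case. For individual markers, which the rule also covers, the bias is small (0.53 for one prespecified) or modest (0.59 for the best of 27).

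Finally, 85/30 is an enrolment count. Recruitment was to continue to February 2021, with analysis after all inclusion data are collected, so the figures for that split show direction only. The hope that later clinical studies will build on this one concerns its results as a whole, not the cutoffs in particular.

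**Conclusion.** The point holds in a limited form. The Statistical Analysis section optimises cutoffs and signatures in one cohort and names no internal validation, so AUC, sensitivity and specificity read from that fit would be too high. At 100/100 the excess in AUC ranges from about 0.02 (selected top 5, true AUC 0.85, a few informative markers) to about 0.21 (all 27, pure noise). It is about 0.03 for one prespecified noise marker. It is larger if the groups stay as unequal as in July 2020.

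These sizes rest on independent markers and a linear combination, both assumed. The direction of the bias does not depend on those choices. The change should be made, but the point does not show that the study's signatures will be spurious.

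**What to change.** In the Statistical Analysis section, state that marker selection, weighting and cutoff choice will all be repeated inside bootstrap resampling or cross-validation. Report optimism-corrected AUC, sensitivity and specificity with intervals as the headline, and label any uncorrected figure *apparent*. Call the cutoffs exploratory until they have been tested in other patients. A penalised model is one option for combined scores, not a requirement.

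The change needs no further patients or assays. It costs some programming time, and the reported accuracy will be lower. Because the main analysis is scheduled after inclusion data are complete, it can be fixed beforehand, except for the coagulation branch, which is already being analysed.

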**Biochemical tests**
Leukocyte, lymphocyte and platelet counts, ferritin, lactate dehydrogenase, troponin, creatine kinase, aspartate aminotransferase, alanine aminotransferase, and creatinine

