## Discussion

This TARGET protocol was designed to standardize the evaluation of cellular and molecular immune biomarkers to evaluate their potential as prognosis tools during COVID-19 infection at different degrees of clinical severity. As the host immune response impacts COVID-19 progression, understanding the behavior of immune biomarkers at the different phases of the illness constitutes a crucial step in the identification of patients who will deteriorate and those who will benefit most from treatment. A simultaneous comprehensive assessment of the different aspects of the immune response was the approach adopted for this protocol.

An early study in China showed that the elevation of certain biomarkers such as D-dimer, together with inflammatory markers including ferritin, was associated with the worst outcomes after SARS-CoV-2 infection [33]. These measurements have been incorporated in some clinical practice centers, but their course during disease and actual value in prognosis are not yet fully described. Higher levels of a series of other interleukins were also described in severe forms of the disease [34], contributing to the concept of a cytokine storm, but their exact significance remains unclear. A thorough evaluation of different immune aspects could help to clarify their role.

Less information regarding the cellular immune response has been published, but its role is progressively gaining more attention from the scientific community, as some evidence notes that humoral immunity does not appear to be sufficiently developed after the first SARS-CoV-2 infection [35]. A simultaneous evaluation of these two kinds of immune responses in the TARGET study could help to understand this interface.

Thromboembolism is a recurrent finding among patients with COVID-19, which has made thromboprophylaxis a vital part of the available supportive treatment options. Unfortunately, there is considerable uncertainty about the degree of coagulation derangement, the possible association with the inflammatory response elicited including neutrophil extracellular traps [36], and the consequences of these alterations [13]. Further knowledge is needed to better understand COVID-19–associated coagulopathy to provide frontline clinicians with better treatment options to manage the ensuing clinical manifestations.

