In summary, TARGET is a translational study that aims to verify the role of cellular and molecular immune biomarkers in the prognosis of COVID-19, opening up avenues for their use in clinical practice. The results that will be achieved are not meant to be restricted to the description of the disease pathophysiology, but to form a basis for future clinical studies that will ultimately help the clinicians on the front line.

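### The stated ROC rule and unadjusted group tests give no comparison with age or routine day-0 data, so a biomarker that mainly tracks them can look informative

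*Protocol article*

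**What the plan says.** The Statistical Analysis section of the protocol article fixes three things that bear on this point.

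- **ROC step.** "Receiver operating characteristic curves will determine cutoff points at which individual or combined scores of the molecular and cellular biomarkers become informative" about progression. The criterion is optimal sensitivity and specificity, and the goal is the signature that best describes each clinical status. No reference model is named.
- **Group comparisons.** Soluble biomarkers are compared by t test or analysis of variance, or by the Mann-Whitney or Kruskal-Wallis test, "with a significance level set at .05". These tests are unadjusted.
- **Other data.** Clinical and demographic variables are compared between severity groups. Relative risks for the main binary outcomes come from a log-binomial model for which no covariates are listed.

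The benchmark data exist. Table 1 records age, gender, comorbidities, time of symptoms and biochemical tests at day 0. Textbox 1 lists the biochemical tests as "Leukocyte, lymphocyte and platelet counts, ferritin, lactate dehydrogenase, troponin, creatine kinase" and others, under a heading separate from the serum immune biomarkers.

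The Discussion states the purpose: the study "aims to verify the role of cellular and molecular immune biomarkers in the prognosis of COVID-19", with use in clinical practice in view. It also reports that D-dimer and ferritin were associated with the worst outcomes in an early study, and says: "These measurements have been incorporated in some clinical practice centers". The same sentence goes on to say that the course of these markers and their real prognostic value are not yet fully described.

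**The concern.** A stand-alone ROC curve shows whether a marker separates severe from nonsevere patients. It does not show whether the marker tells the clinician anything beyond the patient's age, history and routine blood results. A cytokine that rises with age, or moves with ferritin, inherits some of their discrimination and gets an AUC above 0.5 even if it carries no information of its own.

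This matters because the Discussion presents the markers as prognostic tools that could help identify patients who will deteriorate. If the published result is a cutoff or signature whose performance is borrowed from age or routine values, the claim of usefulness does not follow from the analysis.

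**Working it through.** **The plan's own figure.** No figure is stated for the ROC step. The only planned number is 200 patients, which sets the group sizes used below. Its inputs are "20% of patients who are critically ill have elevated TNF-α levels compared to 5% of patients who are noncritically ill" and "Based on a bilateral 95% significance level, a power of 80%, and a case-control ratio of 1".

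- Standard formula: n = [1.960·√(2·0.125·0.875) + 0.842·√(0.20·0.80 + 0.05·0.95)]² / 0.15² = 75.1, so 76 per group and 152 in total.
- With continuity correction: 88 per group and 176 in total.
- At 100 per group, power is about 90%.

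The stated 200 is therefore larger than its inputs require. This is conservative and does not affect the present point.

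**Inputs for the check**

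- From the documents: two-sided 0.05; 200 patients at "a case-control ratio of 1", so 100 severe and 100 nonsevere.
- Assumed, because the documents give neither: the AUC of the benchmark (age or a routine value) for severity, 0.65 to 0.80; and the correlation ρ of the marker with the benchmark, 0.3 to 0.9.

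**Model.** The benchmark is normal with unit variance in both groups and is shifted by d = √2·z(AUC_b) in severe patients. The marker is ρ·benchmark + √(1−ρ²)·noise, so it has no information of its own.

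- Marker shift: d_m = ρ·d
- Marker AUC: Φ(d_m/√2) = Φ(ρ·z(AUC_b))
- Chance of p < .05 at 100 per group: Φ(d_m·√50 − 1.960)
- Sensitivity and specificity at the optimal cutoff, equal in this model: Φ(d_m/2)

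Example with AUC_b 0.70 and ρ 0.5: z = 0.524, d = 0.742, d_m = 0.371. The marker AUC is Φ(0.262) = 0.60, and the chance of significance is Φ(2.622 − 1.960) = 75%.

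**Results: marker AUC, and chance of an unadjusted p < .05**

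| Benchmark AUC | ρ = 0.3 | ρ = 0.5 | ρ = 0.7 | ρ = 0.9 |
|---|---|---|---|---|
| 0.65 | 0.55, 21% | 0.58, 49% | 0.61, 77% | 0.64, 93% |
| 0.70 | 0.56, 35% | 0.60, 75% | 0.64, 96% | 0.68, >99% |
| 0.75 | 0.58, 53% | 0.63, 92% | 0.68, >99% | 0.73, ~100% |
| 0.80 | 0.60, 71% | 0.66, 99% | 0.72, ~100% | 0.78, ~100% |

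The ROC step would return an optimal cutoff in every cell. Sensitivity and specificity at that cutoff run from about 0.53 each (0.65, ρ 0.3) to about 0.70 each (0.80, ρ 0.9).

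**Effect of adjustment.** In 1000 simulated studies per setting (benchmark AUC 0.70 and 0.75; ρ 0.3, 0.5 and 0.7), the Mann-Whitney test was significant in 34% to over 99%. The marker's coefficient in a logistic model that also held the benchmark was significant in 4% to 6%.

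**A second model.** Severity was made logistic in a routine composite with slope 1.5 (population AUC 0.81). A marker with no independent information then had AUC 0.62 at ρ 0.4 and 0.68 at ρ 0.6. Mann-Whitney was significant in about 84% and 99% of studies of 200. The nested likelihood-ratio test was significant in about 5%, and never more than about 7% across repeat runs. With about three-quarters of patients severe, close to the 85 D-branch and 30 T-branch patients reported under Results (85/115 = 74%), the unadjusted rates were 77% and 98%, and the nested rate was again about 5%.

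**The case against.** The strongest reply is that this is an absence in a condensed article. A fuller analysis plan may hold covariate sets and base models, the log-binomial model can carry covariates, and the ROC sentence allows combined scores. A reader might infer that the plan never compares the markers with routine data and that a mirror marker will be declared informative. The documents do not support that. They show only that no comparison is stated and that adjustment is not excluded. What remains is that the article does publish a criterion for informative markers, and that criterion does not answer the question posed in the Discussion.

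Other replies, and what stands of each:

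- **Early-phase aim.** The ROC sentence speaks of characterising clinical status, and the Discussion presents the results as a basis for future studies. Stand-alone discrimination is a legitimate first description, so the curves should stay. It does not carry a claim about prognosis or clinical use.
- **No p-value rule in the ROC step.** Correct. The significance rates above belong to the group tests. For the ROC step, the relevant figures are the AUCs and cutoffs.
- **The routine markers are not an established benchmark.** The Discussion says their prognostic value is not yet fully described. It also calls ferritin inflammatory, so a combined score might include it, though inclusion would not be a benchmark comparison. D-dimer is ticked only at day 9 and cannot enter a day-0 model. None of this applies to age.
- **Over-adjustment.** Ferritin, lactate dehydrogenase and lymphocyte count may lie on the same inflammatory pathway as the markers. Discarding a marker because these already capture it could reject a relevant mediator. This stands and shapes the fix.
- **Outcome.** Branch is set at presentation. A gain in AUC for severity at inclusion shows added discrimination and is not by itself proof of prognosis. This also stands.

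**Conclusion.** The point holds in a limited form. The stated analysis judges biomarkers by stand-alone ROC cutoffs and unadjusted tests. It states no comparison with age, comorbidity, symptom duration or routine laboratory values, all of which are collected at day 0. A marker that largely tracks these can look informative, and a conclusion about prognostic or clinical usefulness would not follow.

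The size depends wholly on associations that the documents do not give. A weak benchmark and a weak correlation produce a misleading group difference in about one study in five. A strong benchmark or a close mirror makes it nearly certain. After adjustment the rate is about the nominal 5% throughout. The change is worth making because the data are already planned and the cost is small.

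**What to change.** Keep the stand-alone ROC curves and label them as descriptive characterisation. Add to Statistical Analysis, for each marker or signature, the likelihood-ratio test and the change in AUC with confidence interval over:

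- **(a)** a prespecified base model of age, sex, comorbidity count and days of symptoms;
- **(b)** as a secondary benchmark, model (a) plus day-0 ferritin, lactate dehydrogenase and lymphocyte count.

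Leave out of both models the variables that define severity in the Clinical Assessment Protocol, such as respiratory rate, oxygen saturation and ventilation. Confirm that lactate dehydrogenase is measured: Textbox 1 lists it, but the analyte list under Clinical Biochemistry and Hematologic Analysis does not.

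Limit claims of prognostic usefulness beyond existing data to markers that add to base model (a), and name the outcome for which the gain was shown. Do not use (b) as a veto on a marker's biological relevance.

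The cost is two extra models per marker, four degrees of freedom for (a) and seven for (b) if each variable enters as one term, and fewer markers that look useful. No visits or assays are added. The article says analysis starts only after inclusion data are complete, so at that stage the rule could still be fixed in advance, except for the coagulation branch, which was already being analysed.
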